### Sample size calculation

The sample size was estimated using the formula for ordered categorical data suggested by John Whitehead, stated below.^22^ The primary outcome measure for the power calculation is the difference in stroke severity on a three-level scale between inactive and physically active patients. Control probabilities were collected from previous research (table 2).^6^ We expect a fraction of 60% physically inactive patients (SGPALS level 1). The sample size estimate was calculated to detect an OR of 2.0 at an alpha level of 0.01 with a power of 80.^6^ Based on the power calculation, we need a minimum of 628 patients with ICH, which is within the expected number of cases.

**Table 2 T2:** Frequencies of stroke severity using the National Institutes of Health Stroke Scale (NIHSS), in physically inactive and active patients with stroke (Reinholdsson *et al*)^6^

	No physical activity $\pi_{C}$	Physical activity $\pi_{E}$	Cumulative OR
Mild stroke (NIHSS 0–5)	73.6%	86.5%	0.44
Moderate stroke (NIHSS 6–14)	20.4%	10.8%	0.43
Severe stroke (NIHSS >14)	6.0%	2.7%	-

$$n=6{\left(Z_{1-\frac{\alpha }{2}}+Z_{\beta }\right)}^{2}/\left(log{\left(OR\right)}^{2}\left[1-\sum_{i=1}^{k}{\left(\left(\pi_{iE}+\pi_{iC}\right)/2\right)}^{3}\right]\right)$$

### Statistical analyses

Data will be analysed using R, V.4.0.2 (R Core Team. R: A language and environment for statistical computing. R Foundation for Statistical Computing, Vienna, Austria.), and SPSS Statistics for Windows, V.27.0 (released on 2018; IBM). All statistical testing will be interpreted at a two-tailed significance level of 0.01 to adjust for multiple comparisons.

### Missing data

Missing observations for each variable will be explored, and variables with more than 30% will be excluded from the data set. Individuals with missing values on more than 20% of the remaining variables will be excluded from analyses. The number of missing observations in the total data set is expected to be below 3%. Multiple imputation by chained equations will be applied to handle missing data. We will use the predictive mean matching method, originally proposed by Rubin,^23^ implemented for multiple imputation.^24^ The method generates a separate model for each variable with missing data, and creates multiple imputations for each value. The predictive mean algorithm preserves the original data distribution and allows for imputation of continuous, binary and categorical data.^25^ The imputation will be performed separately for patients with ICH and ischaemic stroke, and ordered from the variable with least missing values (monotone). Only variables with a minimum correlation of 0.1 and at least 50% data will be used for prediction. The number of multiple imputations will be set to m=20.

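### The 0.1 correlation screen for imputation predictors does not exempt exposure, outcomes or confounders, so it can pull a modest activity effect toward the null; the expected bias is small at the forecast missingness

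*Protocol article*

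**What the plan says.** The Missing data section plans multiple imputation by chained equations with predictive mean matching. On the choice of predictors it states: "Only variables with a minimum correlation of 0.1 and at least 50% data will be used for prediction". It exempts neither the exposure, the outcomes nor the adjustment covariates.

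Three other statements there bear on the point:
- On the amount of missing data: "The number of missing observations in the total data set is expected to be below 3" per cent.
- On the limit for a single variable: "variables with more than 30% will be excluded from the data set".
- On strata: "The imputation will be performed separately for patients with ICH and ischaemic stroke".

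Under Regression models, activity is then related to three-level NIHSS (ordinal regression) and to all-cause mortality (Cox), separately by stroke type and adjusted for the confounders listed at the end of Confounding variables.

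The planning effect is in Sample size calculation: "The sample size estimate was calculated to detect an OR of 2.0 at an alpha level of 0.01 with a power of 80" per cent. The same section gives the exposure split: "We expect a fraction of 60% physically inactive patients (SGPALS level 1").

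**The concern.** An imputation model should contain every variable of the analysis that follows. If SGPALS is imputed without NIHSS, the imputed activity values relate to severity only through the predictors that remain, and the estimated OR moves toward 1. The same holds if death is left out of the SGPALS model, or SGPALS out of the NIHSS model.

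A cut on marginal correlation is a poor test of what belongs in the model. A modest OR on a skewed three-level outcome gives a small correlation, and so does a rare confounder with a real effect.

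There is a second consequence. Both research objectives compare ICH with ischaemic stroke, and imputation is done within stroke type. The screen may keep NIHSS or death as a predictor in one type and drop it in the other. One estimate would then be attenuated and the other not, which could create or hide a difference.

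**Working it through.** **Inputs.** From Table 2: inactive patients 73.6 / 20.4 / 6.0% (mild / moderate / severe); active patients 86.5 / 10.8 / 2.7%. From Sample size calculation: 60% inactive, so 40% active; OR 2.0; alpha 0.01; power 80%. From Data collection and management: 763 patients with ICH. Assumed, because the documents do not give them: an ICH severity split of 40 / 35 / 25% in inactive patients, mortality of 30% to 60% in inactive patients, and the share of SGPALS that is missing.

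**1. The plan's own figure.** Whitehead's formula for unequal groups with ratio A = 60/40 = 1.5 is N = 3(A+1)²(z₁₋α/₂ + z_power)² / (A · ln(OR)² · [1 − Σp̄³]). Here (z sum)² = 11.68, ln(2)² = 0.4805 and 1 − Σp̄³ = 0.4832, so N = 12.5 × 11.68 / (0.4805 × 0.4832) = 628.9. The stated 628 is reproduced and is not affected by this point.

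**2. Does the activity–NIHSS pair pass the screen?** With severity scored 0/1/2, |r| = √(0.4 × 0.6) × (difference in mean score) / SD(score). The active rates come from shifting the inactive cumulative odds by the OR.
- OR 2.0, Table 2 inactive rates: active 84.8 / 12.1 / 3.1%; mean scores 0.324 and 0.183; |r| = 0.490 × 0.141 / 0.541 = 0.128.
- Both Table 2 columns as printed: |r| = 0.490 × 0.162 / 0.534 = 0.149.
- OR 1.5, Table 2 inactive rates: active 80.7 / 15.2 / 4.1%; |r| = 0.490 × 0.090 / 0.556 = 0.079.
- OR 1.4, Table 2 inactive rates: |r| = 0.067.
- Assumed ICH split: |r| = 0.175 at OR 2.0, 0.105 at OR 1.5 and 0.088 at OR 1.4.

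**3. Chance that the sample |r| is below 0.1 (Fisher z, n = 763).** P = Φ[(atanh 0.1 − atanh ρ) × √760].

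| True OR | Table 2 inactive rates | Assumed ICH split |
|---|---|---|
| 2.0 | 22% | 2% |
| 1.5 | 72% | 44% |
| 1.4 | 82% | 64% |

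At ρ = 0.149 the chance is 9%.

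**4. Activity and death.** With assumed inactive mortality of 30% to 60% and active mortality 1 − (1 − p)^HR, |r| is 0.072 to 0.102 at HR 0.75 and 0.057 to 0.080 at HR 0.8.

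**5. A rare confounder.** At an assumed 5% prevalence, with a twofold odds ratio between the condition and inactivity, |r| is 0.067; at 3% prevalence it is 0.053. Both fail the screen.

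**6. Size of the bias if NIHSS is dropped.** Suppose a share m of SGPALS is missing completely at random and is imputed from its marginal distribution. The expected table is (1 − m) × true table + m × product of margins. Fitting the proportional-odds model to it reduces the log OR by about m, so the OR is close to OR^(1−m); for example 1.5^0.97 = 1.48. Fitted values on Table 2 rates:

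| SGPALS imputed | True OR 2.0 | True OR 1.5 |
|---|---|---|
| 3% | 1.96 | 1.48 |
| 10% | 1.86 | 1.44 |
| 20% | 1.73 | 1.38 |
| 30% | 1.61 | 1.32 |

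**7. Does the 3% forecast limit SGPALS itself?** Not strictly. Table 1 lists 23 variables, and an average of 3% is 23 × 3 = 69 percentage points. One variable could be 30% missing if the other 22 averaged (69 − 30)/22 = 1.8%. This shows only what the wording permits.

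**The case against.** The strongest reply is that the plan's own figures point to little harm.

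- **The planned effect passes.** A reader might infer that the rule removes the very association under study. At OR 2.0 the expected |r| is 0.128, or 0.149 from Table 2, so the pair is normally kept. This stands.
- **There is no fixed threshold.** On Table 2 rates |r| crosses 0.1 near OR 1.7, and one might conclude that NIHSS is lost for anything weaker. That would need Table 2, which describes stroke patients in general, to fit ICH, and crude and adjusted associations to be equal. The assumed ICH split already passes at OR 1.5. Confounding by age or comorbidity would raise the crude correlation. One standardised confounder with assumed log-odds slopes of 0.5 (lower activity) and 0.3 (higher severity) lifts 0.079 to 0.103; weaker slopes of 0.3 and 0.2 give 0.089. This stands: the crossing point moves with the assumptions.
- **Little is expected to be missing.** The forecast is below 3% overall, and activity and severity were checked against medical records to limit gaps. Heavy missingness in SGPALS, or more of it in severe strokes, is an inference from self-report; the documents do not state it. This stands.
- **Imputed values need not be empty of association.** Retained covariates carry part of the link between activity and outcome, so the figures in step 6 are upper-end. Death comes from a national register and will hardly need imputing; for mortality the concern is death as a predictor of SGPALS.

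None of this supplies the missing exemption. The rule is worded as exclusive, and a sound imputation model should not depend on whether a sample correlation happens to exceed 0.1.

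**Conclusion.** The point holds in a conditional form. As written, the screen can remove NIHSS, death or confounders from the SGPALS imputation model, and SGPALS from the NIHSS model, which biases the activity effect toward the null. At the planned OR of 2.0 this is unlikely (about 9% to 22% in the ICH sample on Table 2 figures). It becomes a real possibility for ORs around 1.5 or weaker and for mortality HRs around 0.75 or closer to 1.

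If the pair is dropped, a true OR of 1.5 becomes about 1.48 at 3% missing SGPALS, and about 1.44, 1.38 and 1.32 at assumed shares of 10%, 20% and 30%. The last is the most the plan allows and is not something it predicts. These sizes assume data missing completely at random and no association carried by retained covariates. The correlations assume the severity and mortality distributions stated above and no confounding.

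The expected impact is minor at the forecast missingness. The separate imputation by stroke type adds a possible distortion of the ICH–ischaemic comparison, whose size cannot be given from the document.

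**What to change.** State that every imputation model, in both stroke types, includes as predictors whatever their correlation:
- SGPALS and NIHSS;
- the death indicator together with the Nelson–Aalen cumulative hazard;
- all the confounders listed at the end of Confounding variables.

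Apply the 0.1 screen only to auxiliary variables that are in none of the analysis models. Use the same forced set for ICH and ischaemic stroke, so that the two sets of estimates are handled alike. Reporting the missing share of SGPALS and NIHSS by stroke type would let readers judge how much rests on imputation.

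The cost is a change to the predictor matrix in the imputation code and a sentence in the plan. No new data are needed and the sample size is unaffected.

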### Propensity scores and matching

To achieve equipoise between patients with ICH and ischaemic stroke, propensity score matching will be applied. We will include the entire cohort of patients with ICH and match them with consecutive ischaemic stroke patients, in a 1:3 ratio. The propensity score will be based on sex and potential confounding variables. The rational for the selection of confounders is given below. Here, we assume that confounders for the effect of physical activity on stroke severity will be analogous for ICH and ischaemic stroke. We will conduct generalised boosted regression modelling to calculate the propensity scores.^26^ We intend to estimate the average eﬀect of being physically active, that is, the average treatment effect for the treated will be applied. The number of trees, shrinkage and interaction depth will be tuned by using 10-fold cross-validation. We will use the stopping rule es.mean, which uses the absolute standardised bias as balance metric and the mean of the covariate balance metrics to summarise across variables. The propensity score matching will be conducted using the nearest neighbour matching method, with a logistic distance measure and without replacement.^27^

### Regression models

We will conduct separate models for haemorrhagic and ischaemic stroke cases, respectively. All models will be adjusted for potential confounders. The association between prestroke physical activity and admission stroke severity will be evaluated using multivariable ordinal regression models.^28^ For the ordinal regression, NIHSS scores will be trichotomised. A subgroup analysis will be performed for patients with first-time ICH. Prior to the analyses, absence of multicollinearity, and the proportional odds assumption will be checked. Diagnostics will be performed using surrogate residuals.^29^

The association between prestroke physical activity and all-cause mortality will be evaluated using multivariable Cox proportional-hazards models.^30^ Additional models will be fitted adjusted for admission stroke severity.^31^ Model diagnostics will be applied to evaluate violations of the proportional hazards assumption, random censoring and functional forms of continuous covariates.^32^ Furthermore, outlying and influential observations will be checked for all models.

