## Abstract

**Introduction:**

Piling evidence suggests that a higher level of prestroke physical activity can decrease stroke severity, and reduce the risk of poststroke mortality. However, prior studies have only included ischaemic stroke cases, or a majority of such. We aim to investigate how premorbid physical activity influences admission stroke severity and poststroke mortality in patients with intracerebral haemorrhage, compared with ischaemic stroke. A prespecified analysis plan counteract some inherent biases in observational studies, and promotes transparency.

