### Research objectives

(1) To investigate the relationship between prestroke physical activity and admission stroke severity in patients with ICH, compared with patients with ischaemic stroke. (2) To investigate how prestroke physical activity influence the risk of mortality after ICH, in comparison to ischaemic stroke.

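### Both objectives compare the activity effect in ICH with that in ischaemic stroke, but the between-type difference has no planned estimate, confidence interval or test

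*Protocol article*

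**What the plan says.** The Research objectives are comparative. The first concerns activity and "admission stroke severity in patients with ICH, compared with patients with ischaemic stroke". The second is "To investigate how prestroke physical activity influence the risk of mortality after ICH, in comparison to ischaemic stroke". The aim in the abstract uses the same frame: "in patients with intracerebral haemorrhage, compared with ischaemic stroke".

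The design follows from this. Under Propensity scores and matching, the whole ICH cohort is matched 1:3 to ischaemic stroke patients, for this reason: "To achieve equipoise between patients with ICH and ischaemic stroke, propensity score matching will be applied".

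The analysis is set out under Regression models: "We will conduct separate models for haemorrhagic and ischaemic stroke cases, respectively". Severity gets an ordinal model and mortality a Cox model, each adjusted for confounders. Under Statistical analyses: "All statistical testing will be interpreted at a two-tailed significance level of 0.01". Under Sample size calculation, the powered contrast is active against inactive, counted in ICH patients only: "Based on the power calculation, we need a minimum of 628 patients with ICH". The final ICH sample is given as 763 under Data collection and management.

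**The concern.** The planned output is one OR and one HR for ICH and one of each for ischaemic stroke. Nothing in the article turns each pair into an answer to the comparative question. Without a planned contrast, the natural way to read the results is to see which of the two reaches 0.01. That is not a comparison of effects. The ischaemic group is three times as large, so its estimate is more precise and will cross the threshold more often even when the effects are identical.

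The likely misreading therefore has a direction: a common effect reported as present in ischaemic stroke and absent in ICH. The Introduction says that no earlier study has examined the ICH subgroup, so there would be little to correct such a reading. The article also argues that prespecification is what protects observational work from bias, and a contrast chosen after both sets of results are known would lack that protection.

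**Working it through.** **Inputs.** From the article: 763 ICH patients; 1:3 matching, hence 3 × 763 = 2289 ischaemic patients; 60% inactive, so allocation ratio A = 60/40 = 1.5; two-sided alpha 0.01 (z = 2.576); power 80% (z = 0.842); design OR 2.0; Table 2 severities of 73.6/20.4/6.0% (inactive) and 86.5/10.8/2.7% (active).

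**The plan's own figure.** Whitehead's formula with unequal allocation is N = 3(A+1)²(z₁+z₂)² / (A·log(OR)²·U), with U = 1 − Σp³. The simple mean of the two Table 2 columns is 80.05/15.6/4.35%, which gives U = 0.4832. Then 3 × 2.5² / 1.5 = 12.5, and N = 12.5 × 11.679 / (0.4805 × 0.4832) = 628.9. The stated 628 is reproduced, and it concerns the activity effect within ICH only.

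**Precision in each type.** The same formula gives SE(log OR) = √(12.5 / (N·U)). Here p is the 60/40 weighted mix of the inactive column and that column shifted by OR 2.0 (84.8/12.1/3.1%), that is 78.1/17.1/4.8%, so U = 0.519. Applying this distribution to both stroke types is an assumption, since Table 2 describes stroke patients without splitting by type.

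- ICH: √(12.5 / (763 × 0.519)) = 0.178
- Ischaemic stroke: √(12.5 / (2289 × 0.519)) = 0.103
- Difference of the two log ORs, treating the groups as independent: √(0.178² + 0.103²) = 0.205

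**How often the two tests disagree when the true OR is the same.** Power in each type is P = Φ(log OR / SE − 2.576), and disagreement is P₁(1−P₂) + P₂(1−P₁). U is held at its OR 2.0 value. As a sensitivity check, inactive ICH patients are given an assumed flatter split of 40/30/30 (U = 0.859, SE 0.138), with ischaemic stroke unchanged.

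| Common OR | Power, ICH | Power, ischaemic | Tests disagree | Tests disagree, flatter ICH split |
|---|---|---|---|---|
| 1.5 | 38% | 92% | 60% | 38% |
| 1.75 | 72% | 99.8% | 28% | 7% |
| 2.0 (design) | 91% | >99.9% | 9% | 0.7% |

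At OR 1.5, 56 of the 60 percentage points are the pattern ischaemic significant, ICH not: 0.916 × (1 − 0.385) = 0.56. With the simple mean of the Table 2 columns (U = 0.4832) in place of the weighted mix, disagreement is 61%, 32% and 12%.

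**What a formal contrast could detect.** The ratio of ORs detectable with 80% power at 0.01 is exp((2.576 + 0.842) × SE of the difference).

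- Main assumptions: exp(3.418 × 0.205) = 2.02
- Simple mean of Table 2 (SE 0.213): 2.07
- Flatter ICH split (SE 0.172): 1.80

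The range is therefore about 1.8 to 2.1. With SE 0.213, power is 75% for a ratio of 2.0 and 25% for a ratio of 1.5.

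**Mortality.** No event rate is stated, so no corresponding figure can be given for the Cox models.

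**The case against.** The strongest reply is that the ICH effect is itself the new question. The Introduction stresses the lack of ICH data, the sample size is built on ICH patients, and the separate models estimate that effect with adjustment. This stands. A reader might infer that the study's main question gets no estimate at all, but the article does not support that: what lacks an estimate is the difference between types.

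A reader might also infer that the plan intends to compare types by significance in one and not in the other. It does not say so. It sets a 0.01 threshold and is silent on how the two results will be compared, so the fallacy is a risk left open and not a prescribed method. Nor is it right that a difference could never be shown. The two models use different patients, so a contrast can be formed from their estimates with an approximate SE; it would simply be unplanned.

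The size of the problem also depends on the true effect. At the design OR of 2.0 disagreement is only about 9%, and under 1% with the flatter split, so a misleading pattern is common only for effects smaller than the one planned for.

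Finally, separate models have a real advantage. A pooled ordinal model with a single stroke-type term forces one proportional-odds shift between types. Setting 73.6/20.4/6.0 against 40/30/30 gives cumulative ORs of (0.736/0.264)/(0.40/0.60) = 4.2 and (0.94/0.06)/(0.70/0.30) = 6.7, which would break that assumption. The repair should not impose it.

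None of this supplies the missing contrast. Nor can the gap be put down to detail held elsewhere: the article presents itself as the statistical analysis plan and states the model structure outright.

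**Conclusion.** The concern holds in this form: both objectives name a comparison between stroke types, the matching is built for it, and the planned models give no estimate, confidence interval or test of it, for severity or for mortality. The effects within each type remain validly planned, and the ICH severity effect is adequately powered at the design OR.

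If the true OR is common to both types, reading the two 0.01 tests side by side would suggest a spurious difference in about 60% of studies at OR 1.5, 28% at 1.75 and 9% at 2.0, or 38%, 7% and under 1% with the flatter ICH split. These figures are unadjusted and assume 763 and 2289 patients, 60% inactive in both types, Table 2 severities where not stated otherwise, and independence between the groups. They apply to severity only.

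**What to change.** Keep the separate models, with the ICH severity model as the powered analysis. For each outcome, prespecify the activity-by-stroke-type contrast: a ratio of ORs for severity and a ratio of HRs for mortality, each with a 99% CI.

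Obtain it as the difference of the log estimates from the two models. Equivalently, fit a joint model with thresholds (ordinal) or baseline hazards (Cox) specific to stroke type and with confounder-by-type terms, so that no common shift between types is imposed. Use SEs that account for the matched sets, and pool over the 20 imputations.

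State that any claim of similar or different effects rests on this contrast alone, and that for severity it has 80% power at alpha 0.01 only for a ratio of ORs of about 1.8 to 2.1. Smaller differences should be reported as an estimate with its interval, and a non-significant contrast should not be read as evidence of equal effects.

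The cost is one extra contrast per outcome on data already received, and a less favourable power statement for the comparison than the one now given for ICH alone.

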### Data collection and management

Prestroke physical activity and acute stroke severity assessments were collected from the Väststroke register, and cross-references with medical records to minimise missing data. Physical activity was assessed using the four-level Saltin-Grimby Physical Activity Level Scale (SGPALS).^18 19^ Acute stroke severity was assessed using the National Institutes of Health Stroke Scale (NIHSS).^20^ The data collected from the Väststroke register has been sent for merging with national registries. Information regarding prestroke conditions and treatments will be collected from the Swedish National Stroke Registry (Riksstroke). Country of birth will be collected from the Swedish Multi-Generation register, and socioeconomic variables will be collected from the Longitudinal Integration Database for Health Insurance and Labour Market Studies held by Statistics Sweden. Comorbidities will be collected from the National Patient Registry, and mortality rates will be collected from the Swedish Cause of Death registry, held by the National Board of Health and Welfare. All-cause mortality and cerebrovascular mortality will be recorded for all patients until October 2021, which allow for a minimum follow-up of 2 years.

The data management started on 17 May 2021 after submission of this protocol. The final data was recived on 19 October 2021. Patients without a Swedish personal identification number, and patients with non-specified aetiology will be excluded. The final sample is will consist of 763 patients with ICH.

Continuous variables will be either mean-centred or dichotomised when appropriate. For ordinal variables, categories with limited observations will be merged on the base of clinical reasoning. All variables and data sources are listed in table 1. The categories of SGPALS will be collapsed into inactive (SGPALS level 1) and physically active (SGPALS levels 2–4) for all analyses. NIHSS scores will be categorised based on distributional assumptions.^6^ The weighted Charlson Comorbidity Index will be calculated, and applied as a four-level ordinal variable using the ICD-10 diagnoses specified in table 1. The 1-year mortality risk described by Charlson *et al* was 12% for patients with 0 points, 26% for 1–2 points, 52% for 3–4 points and 85% for ≥5 points.^21^

**Table 1 T1:** Registers and variables included in the study

The väststroke register	
Age	Mean centred or dichotomised.
Sex	Female/male.

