Physical activity assessment (SGPALS)	Mostly sedentary (level 1); light physical activity such as walking ≥4 hours/week (level 2); moderate physical activity such as running ≥2 hours/week (level 3); hard physical training for competition sports several times per week (level 4).
Stroke severity assessment (NIHSS)	Mild stroke (NIHSS 0-5), moderate stroke (NIHSS 6-14), and severe stroke (NIHSS >14).

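### The severity-adjusted mortality models have no stated NIHSS coding, and the only coding the article defines, three bands, would leave a modest part of the severity pathway in the activity hazard ratio

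*Protocol article*

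**What the plan says.** The Regression models section evaluates activity and all-cause mortality with confounder-adjusted Cox models and then adds: "Additional models will be fitted adjusted for admission stroke severity". The form of the severity covariate is not given there.

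Two other places deal with the coding of NIHSS. Data collection and management says, without limiting it to one model: "NIHSS scores will be categorised based on distributional assumptions". Table 1, which lists the form of each variable, gives only "Mild stroke (NIHSS 0-5), moderate stroke (NIHSS 6-14), and severe stroke (NIHSS >14", whereas age and income may be either centred or split in two.

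Two phrases in Regression models leave room for another form: "For the ordinal regression, NIHSS scores will be trichotomised", and the planned Cox diagnostics for "random censoring and functional forms of continuous covariates". Neither names a different coding of NIHSS.

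The stroke types are analysed apart ("We will conduct separate models for haemorrhagic and ischaemic stroke cases, respectively"), while the second objective is comparative: "To investigate how prestroke physical activity influence the risk of mortality after ICH, in comparison to ischaemic stroke".

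**The concern.** This is about NIHSS as a covariate in the Cox models, not as the ordinal outcome. Under the first objective, severity may itself be affected by activity. If it is, active patients will tend to score lower inside each band as well as being more often in a lower band, above all in the open-ended top band. Indicators for three bands hold the band constant, not the score. Whatever mortality difference goes with the within-band score difference is credited to activity.

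The error has a direction. If activity were related to death only through a milder stroke, the banded model would still tend to give a hazard ratio somewhat below 1. Anyone comparing the models with and without severity would then overstate what is left after severity is accounted for.

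**Working it through.** **The article's own figure.** The only computed figure is the minimum of 628 patients with ICH. With z = 2.576 + 0.842, OR 2.0 and the Table 2 probabilities, the mean proportions are 0.8005, 0.156 and 0.0435, and 1 − Σp³ = 0.483. The printed formula gives 6 × 3.417² / (0.693² × 0.483) ≈ 302 per group, 604 in total. The unequal-allocation form, with A = 0.6/0.4 ("We expect a fraction of 60% physically inactive patients (SGPALS level 1"), replaces 6 by 3(A+1)²/A = 12.5 and gives 628.9 in total, which agrees with 628. That figure concerns the ordinal severity outcome and does not depend on how NIHSS enters the Cox models.

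**Check of the banded covariate.** The documents give no NIHSS score distribution, no severity mix for ICH and no NIHSS–mortality slope. Two simulations with different assumptions were therefore used. Both have 40% active, no direct effect of activity (true direct HR 1.00), a log hazard linear in NIHSS, and no confounding or measurement error.

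*Simulation A* (600,000 patients per scenario)
- NIHSS follows a proportional-odds shift with OR 2.0. Scores are uniform within the two lower bands and decline exponentially above 14.
- Deaths are Weibull (shape 0.5), follow-up is 2.3–6.9 years, and the HR is 1.06–1.12 per point.
- Example, mix 45/25/30 and HR 1.09 per point: HR 0.779 without severity, 0.966 with bands, 0.998 with the full score. Share left = ln 0.966 / ln 0.779 = 0.0346/0.2497 = 14%.
- All scenarios: HR 0.95–0.98 with bands and 0.99–1.01 with the full score. Share left is 10–17% for assumed ICH-like mixes (45/25/30 or 35/30/35) and 21–26% for the Table 2 inactive mix.
- Chance of a false finding at the 0.01 level: 1.1–1.7% with 763 patients and 1.3–3.2% with 3 × 763 = 2,289.

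*Simulation B* (400,000 patients per scenario)
- NIHSS is an overdispersed count. The inactive mean is 4.3 (ischaemic-like, close to Table 2), 8 or 12 (ICH-like), and the active mean is 0.6 times that.
- Deaths are exponential, with five years of follow-up.
- Bias = log HR with bands − log HR with full score. Share left = bias / (log HR without severity − log HR with full score). Standard errors are scaled to 2,289 (ischaemic-like) or 763 (ICH-like).

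| Setting | Slope per point | HR, no severity | HR, bands | HR, full score | Share left | Bias | SE | Bias/SE (absolute) |
|---|---|---|---|---|---|---|---|---|
| Ischaemic-like | 0.05 | 0.893 | 0.967 | 0.984 | 18.3% | −0.018 | 0.079 | 0.23 |
| | 0.08 | 0.852 | 0.965 | 0.992 | 18.4% | −0.028 | 0.076 | 0.37 |
| | 0.12 | 0.818 | 0.966 | 1.009 | 20.7% | −0.044 | 0.072 | 0.61 |
| ICH-like, mean 8 | 0.05 | 0.849 | 0.969 | 1.000 | 19.4% | −0.032 | 0.116 | 0.28 |
| | 0.08 | 0.794 | 0.954 | 1.001 | 20.5% | −0.047 | 0.109 | 0.43 |
| | 0.12 | 0.752 | 0.936 | 0.993 | 21.5% | −0.060 | 0.103 | 0.58 |
| ICH-like, mean 12 | 0.05 | 0.799 | 0.942 | 0.998 | 25.7% | −0.057 | 0.110 | 0.52 |
| | 0.08 | 0.748 | 0.920 | 0.998 | 27.9% | −0.080 | 0.102 | 0.78 |
| | 0.12 | 0.727 | 0.916 | 1.003 | 28.1% | −0.090 | 0.096 | 0.94 |

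The true full-score HR is 1, so its scatter (0.98–1.01) is simulation error. The bias is taken as a difference between two models fitted to the same data.

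**ICH against ischaemic stroke.** In A the ICH-like settings keep a smaller share (10–17% against 21–26%). In B they keep a larger one, by 21.5 − 20.7 = 0.8 to 27.9 − 18.4 = 9.5 percentage points at equal slope. The order depends on the assumed score distribution.

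**The case against.** The strongest reply is that the article never says the Cox models use bands. Trichotomising is tied to the ordinal regression, a qualifier that would be needless if NIHSS were banded everywhere, and the planned check of continuous covariates would fit a continuous NIHSS. This stands in part. Use of the bands is a strong inference, not an express statement. But no other form appears anywhere, and the sentence on categorising is unrestricted. Someone following the article would reach for the bands.

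Second, these are supplementary models and the article does not call them a mediation or direct-effect analysis. This stands. A reader might infer that the plan would report a false survival benefit independent of severity. The documents state no such interpretation, and a false significant result remains uncommon: at most 3.2% against a nominal 1%.

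Third, both simulations make the log hazard linear in NIHSS with no measurement error, which favours the full score. This also stands. It is a reason to use a flexible term rather than a straight line, and the near-complete removal shown here is a best case. That mortality rises within the top band is likewise an assumption, not something the documents report.

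**Conclusion.** The concern holds in a limited form. Three bands are the only form of NIHSS the article defines, and the severity-adjusted Cox models are given no other. If the bands are used there, roughly 10–28% of a severity-mediated log hazard ratio stays with activity. With no direct effect, the hazard ratio is then about 0.92–0.98, leaning towards benefit. These figures rest on assumed severity distributions and slopes. The bias was 0.23 to 0.94 of a standard error in Simulation B, so it is modest. The main mortality model, without severity, is not affected, and nor is the sample size.

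A reader might also infer that the two stroke types would falsely appear to differ in their severity-adjusted associations. The remainder could differ between them, because it depends on the severity distribution. The documents do not support saying by how much or which way: the two simulations order the types oppositely, no ICH severity mix is given, and Table 2 describes patients with stroke, not ischaemic stroke specifically.

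**What to change.** In Regression models, after the sentence on the additional models, state: *In the severity-adjusted Cox models NIHSS is entered as the full score with a restricted cubic spline; the same models with the three bands are a sensitivity analysis.* The ordinal outcome model keeps its three categories.

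No new data are needed, since the bands are derived from the score. A spline with four or five knots uses 3 or 4 degrees of freedom. That is two or three more than a linear term (1), and one or two more than the bands (2). The choice should be fixed before the mortality models are fitted.
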